#### **9.4 Sample size calculation**

No relevant studies have previously described the effect of structured exercise on FDP related pain. There has been only one study that evaluated FDP related pain quantitatively. A randomized controlled study performed by Adachi et al. reported the effects of aromatherapy massage on FDP related pain after vitrectomy. Based on the clinical assumption that structured exercise program would have comparable or greater effect on FDP related pain, we conducted a sample size calculation using data from the previous report. We conducted a sample size calculation expecting an effect size of 0.9 based on post-treatment back pain score in aromatherapy group and control group of the previous study. The estimated sample size was 32 patients per group to detect differences between two groups at 90% power and a significance level of 0.05. Considering a 10 % loss to follow-up, we are aiming to recruit 35 patients in each arm.

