### 14. Outcome measures and statistical analysis

#### 14.1. Primary outcome

Pain score measured by numeric rating scale at back neck, shoulder, and lower back on the postoperative day 3. Numeric rating scale is a score that measures pain. If there is no pain, it is marked as 0, and if the pain is the worst possible pain, it is measured as 10.

[figure not shown]

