**14.3. Statistical analysis**

Descriptive statistics for continuous variables will be presented in terms of mean, median, standard deviation, interquartile range, minimum and maximum values, and descriptive statistics for categorical variables are presented in terms of frequencies and ratios belonging to each category.

The comparison of continuous variables between the two groups will be tested with the two-sample t-test or Wilcoxon's rank sum test depending on whether the data are normal, and the comparison of categorical variables will be tested with the Chi-square test or Fisher's exact test. Since there will be three site for pain scoring, the statistical significance will be set at  $p < 0.017$  (0.05 divided by 3, Bonferroni's method) to control the inflation in the size of the type 1 error.

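### Section 9.4 claims 90% power at a significance level of 0.05, but each primary pain site is tested at 0.017, so 32 evaluable per group gives about 85 to 87% per site

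*Protocol*

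**What the plan says.** Section 9.4 gives the sample size basis. The authors were "expecting an effect size of 0.9 based on post-treatment back pain score" in a trial of aromatherapy massage, and conclude: "The estimated sample size was 32 patients per group to detect differences between two groups at 90% power and a significance level of 0.05". They then allow for attrition: "Considering a 10 % loss to follow-up, we are aiming to recruit 35 patients in each arm". The section names neither the test nor whether it is one- or two-sided, and does not say which comparison the 90% refers to.

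Section 14.1 defines the primary outcome: "Pain score measured by numeric rating scale at back neck, shoulder, and lower back on the postoperative day 3". That is three scores per patient.

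Section 14.3 sets the decision rule. Groups are compared by a two-sample t-test or Wilcoxon's rank sum test, depending on normality. "Since there will be three site for pain scoring, the statistical significance will be set at" p < 0.017, explained as "0.05 divided by 3, Bonferroni's method) to control the inflation in the size of the type 1 error".

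**The concern.** The protocol fixes two different significance levels for the same comparison: 0.05 when sizing the trial and 0.017 when analysing it. This is not a detail that could wait for a statistical analysis plan, because both figures stand in the protocol. A smaller significance level with the same sample and effect means less power, so the 90% in section 9.4 may describe a test that section 14.3 does not perform.

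Type I error and the treatment estimates are not affected. What is at stake is the accuracy of the stated power, and how a non-significant result at one site would later be read. A reader relying on section 9.4 would take the risk of missing a true effect of 0.9 at a given site to be 10%.

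**Working it through.** **Inputs**
- Effect size d = 0.9, power 90%, significance level 0.05, 32 per group, 35 recruited per arm, 10% loss: section 9.4.
- Allocation 1:1: section 9.5.
- Three primary sites: section 14.1.
- Level per site 0.05/3 = 0.0167 (printed as 0.017), t-test or Wilcoxon: section 14.3.
- Assumed, because not stated: two-sided tests. For Wilcoxon, the sample size is multiplied by its efficiency relative to the t-test: 0.955 (3/π) for normal data, 0.864 as the conservative minimum.

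**Step 1. Reproduce the stated 32 at two-sided 0.05**

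Normal approximation: n = 2(z₁₋α/₂ + z₁₋β)²/d² = 2(1.960 + 1.282)²/0.81 = 25.9, so 26 per group. The other methods give:

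| Method at two-sided 0.05 | n per group for 90% |
|---|---|
| Exact t-test | 26.94, so 27 |
| Wilcoxon, efficiency 0.955 | 28.2, so 29 |
| Wilcoxon, efficiency 0.864 | 26.94/0.864 = 31.2, so 32 |

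The last row reproduces 32 from the stated effect size, power and level. Whether it was the method used is an inference. A t-test at two-sided 0.025 also gives 32 (31.9), but that level appears nowhere in the protocol. One-sided 0.05 gives 22 to 26, which does not match.

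**Step 2. Power of the test that section 14.3 specifies**

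For the t-test with n per group: noncentrality = d√(n/2), degrees of freedom = 2n − 2. With n = 32 these are 0.9 × √16 = 3.6 and 62. The two-sided critical value is 1.999 at 0.05 and 2.461 at 0.05/3, so power falls from 94.3% to 86.9%. For Wilcoxon, n is replaced by n × efficiency.

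| Evaluable per group, two-sided 0.05/3 | t-test | Wilcoxon 0.955 | Wilcoxon 0.864 |
|---|---|---|---|
| 31 | 85.6% | 83.7% | 79.0% |
| 31.5 | 86.3% | 84.4% | 79.8% |
| 32 | 86.9% | 85.0% | 80.6% |
| 35 | 90.2% | 88.6% | 84.6% |
| n needed for 90% | 34.8, so 35 | 36.5, so 37 | 40.3, so 41 |

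Using the printed 0.017 in place of 0.0167 changes the powers by about 0.2 points. A simulation of the Wilcoxon test with normal data (20,000 runs, n = 32, level 0.017) gave 84.8%, in line with the 0.955 column.

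**Step 3. Attrition**

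35 × 0.9 = 31.5, just under 32. Adding 10% gives 32 × 1.10 = 35.2, reported as 35; dividing by 0.9 gives 35.6, so 36. The two conventions differ by one patient per arm.

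**Step 4. What the 90% could refer to**

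If all three sites truly had d = 0.9 (assumed) and between-site correlations were 0.3 to 0.7 (assumed), then with 32 per group and t-tests at 0.05/3 the chance of at least one significant site is 96 to 99%.

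**The case against.** The strongest reply is that section 9.4 never says the power is per site. Bonferroni supports a claim on any one site, and Step 4 puts the chance of at least one significant site above 90%. That is correct under its assumptions, but it does not rescue the stated figure. The sizing rests on a single back pain score, which is a one-comparison calculation. The protocol gives no effect size for neck or shoulder and no between-site correlation, so an any-site power cannot be derived from it. What stands is that the shortfall must be described as per site.

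A reader might also infer that 32 is an arithmetic error, since a t-test at two-sided 0.05 needs only 27. The documents do not support that. Section 9.4 names no test, section 14.3 permits the rank sum test, and a minimum-efficiency rank sum calculation returns exactly 32. The 0.9 may also be rounded: at 0.949 a t-test at 0.05/3 needs 32, so it cannot be proved from the page that the correction was left out of the calculation. That would still leave section 9.4 stating a level of 0.05. If minimum-efficiency Wilcoxon was the method, the same method at 0.05/3 needs 41, and 32 gives 80.6%, so this explanation enlarges the shortfall.

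Nor is 35 an inflation error. It follows from the common add-10% convention.

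Finally, a loss of a few points is small beside the uncertainty of an effect size borrowed from another intervention. That is fair, and it is why the remedy is to restate the power rather than enlarge the trial.

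**Conclusion.** The point holds for power per site. Section 9.4 states 90% at 0.05, while the primary tests run at 0.05/3. With 32 evaluable per group, power per site is about 87% (t-test) or 85% (Wilcoxon, 0.955), falling to about 81% at minimum Wilcoxon efficiency. Only the t-test with all 35 recruited patients evaluable just reaches 90%, and that leaves nothing for the 10% loss.

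This assumes two-sided tests, a true effect of exactly 0.9 at the site concerned, and the efficiency approximation for Wilcoxon, which ignores ties on the 0 to 10 scale. It does not mean that 32 was miscalculated, that 35 is wrong, or that all three sites must succeed; sections 14.1 and 14.3 set no such requirement. The origin of 32 remains unverifiable until the test and sidedness are named. The figure is wrong as written for the analysis planned, by a modest amount, and is cheap to correct.

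**What to change.** Rewrite the sample size paragraph in section 9.4 so that it uses the level in section 14.3, names the test and sidedness, and says what the power refers to. For example:

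> Each of the three primary pain sites is tested at two-sided 0.05/3. Assuming a standardised difference of 0.9, taken from back pain only and assumed to apply to each site, 35 recruited per arm with 10% loss (31 to 32 evaluable) gives about 86 to 87% power per site with the t-test and about 84 to 85% with the Wilcoxon test (efficiency 0.955). For 90% per site, 35 evaluable per group would be needed with the t-test, or 37 with the Wilcoxon test.

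Add how 32 was obtained, including any Wilcoxon efficiency used, and note that 35 less 10% leaves 31.5.

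The cost is one paragraph and a stated power lower by about 3 to 6 points. No extra patients are required. If the sponsor prefers to keep 90% per site after 10% loss, the recruitment target would be 35/0.9 = 38.9, so 39 per arm (t-test), or 37/0.9 = 41.1, so 42 per arm (Wilcoxon, 0.955).

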#### **9.5 Patients assignment and randomization**

Eligible candidates will be invited to participate and to sign the consent form prior to surgery. After then, the block randomization method with block size of 4 or 6 will be implemented by an independent clinical trial consultant. Randomization will be performed using an online randomization service implemented by Sealed Envelope. Subjects will be allocated randomly 1:1 to either exercise group or control group based on pre-allocated codes placed in sealed opaque envelopes that were opened during the randomization step by a trial coordinator. Based on the code, each subject will be randomized to either the control group or the exercise group.

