### **9.2 Subject exclusion criteria**

- (1) Patients with pre-existing musculoskeletal disorder.
- (2) patients with poor visual acuity in the opposite eye (best-corrected visual acuity less than 20/200 by snellen chart) making patients hard to get the exercise training.
- (3) Patients with posture prescriptions other than the prone position

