#### **9.6 Masking**

Due to the nature of the intervention, participants and researchers cannot be blinded to group allocation. The treating healthcare professionals (i.e. the Research Nurse and Clinical Research Fellow) will also not be masked due to nature of the service. The surgeon will be masked to allocation. The data manager and trial statistician will be masked to allocation throughout the study.

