## 11. Research method

This study is for patients who are going to be prescribed facedown posture after retinal surgery.

Participating the study or not will not influence the clinical decision and surgical procedure, but only a pain assessment in the back neck, shoulder, and lower back will be additionally performed every day after the surgery for the study participants. Those who are assigned to the exercise group will additionally be instructed for a structured exercise program designed to keep the prone posture easily and to relieve musculoskeletal pain. The exercise group will be trained by an exercise therapist. All inpatient care and surgical procedures other than learning and performing rehabilitation exercise will be the same in both study groups.

| Control group                                                                                      | Exercise group                                                                                                                                                              |
|----------------------------------------------------------------------------------------------------|-----------------------------------------------------------------------------------------------------------------------------------------------------------------------------|
| After surgery, take and maintain facedown posture without getting additional training or exercise. | After surgery, subjects will be trained for a structured exercise routine by an exercise therapist and perform the exercise according to the instruction three times a day. |
| Pain assessment will be performed every day after surgery.                                         |                                                                                                                                                                             |

All patients scheduled for vitreoretinal surgery for macular hole or retinal detachment is going to be admitted to the hospital the day before surgery (day 1). On the day 1, every patients will be evaluated for their eligibility, and those who are eligible candidates will be provided with information about the trial and invited to participate. They will be given enough time to consider their decision and the opportunity to ask questions. After informed consent is obtained, subjects will be randomized.

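### Small block sizes printed in the protocol, with recruiting-side staff unmasked, let the next arm be guessed about 69% of the time; hide the parameters and release codes centrally

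*Protocol*

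**What the plan says.** Protocol Section 9.5 states that "the block randomization method with block size of 4 or 6 will be implemented by an independent clinical trial consultant", and that "Subjects will be allocated randomly 1:1 to either exercise group or control group". It names no stratification factor and no rule for mixing the two sizes. It describes two release mechanisms without saying how they fit together: "Randomization will be performed using an online randomization service implemented by Sealed Envelope", and "pre-allocated codes placed in sealed opaque envelopes that were opened during the randomization step by a trial coordinator".

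Section 9.6 says that "participants and researchers cannot be blinded to group allocation", and adds: "The treating healthcare professionals (i.e. the Research Nurse and Clinical Research Fellow) will also not be masked". The surgeon, the data manager and the trial statistician are masked.

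Section 11 names one hospital. It places eligibility, invitation, consent and randomisation on the day before surgery, in that order: "After informed consent is obtained, subjects will be randomized". Only the exercise arm is visited by a therapist, so assignments are visible on the ward. One exclusion in Section 9.2 reads "Patients with pre-existing musculoskeletal disorder", with no further definition there.

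The primary outcome (Section 14.1) is a 0–10 self-reported pain score at three sites on postoperative day 3. Section 14.3 compares groups by a two-sample t-test or rank-sum test at p < 0.017. Section 9.4 aims at 35 patients per arm.

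**The concern.** Opaque envelopes hide the next code but not the running count of past codes. In a short balanced block that count carries information: once one arm is ahead, the other is more likely to come next. Everything needed to use it is available to unmasked staff, namely the past assignments, a single apparent sequence, and the two block sizes printed in the protocol they work from.

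The guess can be made before a patient is invited, and the decision to enrol includes a judgement that bears on the outcome, because an existing musculoskeletal complaint is related to later neck, shoulder or back pain. If that judgement leans, even unknowingly, with the expected arm, the groups differ before treatment starts. The outcome is self-reported, the planned comparison is unadjusted, and no pain score is scheduled before surgery, so such a difference would pass into the primary result.

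**Working it through.** The protocol gives no figure for predictability, so there is none to reproduce.

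**Inputs.** Block sizes 4 and 6, 1:1, no strata (9.5); 2 × 35 = 70 patients (9.4); test level 0.05/3 per site (14.3). Assumptions: one sequence; all past assignments known to the guesser; for the mixed case, sizes drawn 50:50 at random, with the set of sizes known but not their order.

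**One known size throughout (exact).** The guess is the arm with more codes left, and a coin toss when equal.
- Size 4: chances of being right at positions 1–4 are 1/2, 2/3, 2/3, 1. The mean is 2.833/4 = 70.8%. Certain at position 3 with probability 1/3 and always at position 4: (1/3 + 1)/4 = 33.3%.
- Size 6: 0.5, 0.6, 0.6, 0.7, 0.7, 1. The mean is 4.1/6 = 68.3%. Certain with probability 0.1, 0.4 and 1 at positions 4, 5 and 6: 1.5/6 = 25.0%.

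**Sizes mixed at random (4,000 simulated lists of 70, Bayesian updating over hidden block boundaries).**
- Correct guesses: 69.1%.
- Next arm known with probability 0.75 or more: 48.8% of assignments.
- Next arm certain: about 5.5%.

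The simple rule of betting on the arm that is behind, which needs no block sizes, also gives 69.1%. Mixing therefore removes most certain predictions but hardly changes the average guess rate. Modestly larger blocks help little by the same rule: 4/6/8 mixed 68%, 6/8/10 mixed 66%.

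**Possible bias.** Suppose patients entered at slots predicted as exercise have true pain lower by a shift of s SD than those entered at slots predicted as control, with no steering at tied slots. If g is the guess rate, the bias in favour of exercise is about s × (2g − 1).
- Steering at every untied slot (about 61% of slots): 2 × 0.691 − 1 = 0.382. For s = 0.5 the bias is 0.19 SD; for s = 1.0 it is 0.38 SD. The simulated chance of a false favourable result at one site is about 5% and 17%, against 0.05/3/2 = 0.8% nominal.
- Steering only when the next arm is certain: the bias is about s × 0.055, or 0.03 SD and 0.05 SD. The false favourable rate is about 1% and just under 2%.

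**A less predictable scheme.** Big-stick randomisation tosses a fair coin unless the imbalance has reached its limit. With limit 6 over 70 patients, betting on the arm that is behind is right about 53% of the time, the bias under the same two shifts stays below 0.1 SD, and the false favourable rate is below 2%. About 7% of assignments are certain if the limit is known. The largest final split is 38 against 32, with effective size 2 × 38 × 32/70 = 34.7 per arm against 35.

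**The case against.** The plan has real safeguards: an independent consultant, two block sizes, opaque envelopes, and randomisation only after consent. Permuted blocks of mixed size are conventional, and the envelopes are not a fault in themselves. Section 11 has every patient admitted for this surgery assessed and eligible ones invited, with surgery the next day, so there is little room to defer anyone to a later slot; selective exclusion and the order of same-day admissions remain. The protocol does not say who screens or invites. There is no preoperative pain score to steer on. All of this stands, and it limits how much of the predictability could turn into bias.

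It does not remove the predictability. The safeguards protect the code, not the inference from the tally, and consent before opening does not help if the guess precedes the invitation.

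A reader might infer more than the text supports:
- That the trial is fully open. It is not: Section 9.6 masks the surgeon, data manager and statistician.
- That envelopes are held by local trial staff. Section 9.5 says only that a trial coordinator opens them; custody and location are not described.
- That the next arm is usually known. With sizes mixed at random, only about one assignment in eighteen is certain.
- That a bias of 0.19–0.38 SD is to be expected. Those figures need a recruiter who steers by the assumed amount at every untied slot, and nothing in the protocol shows such steering.
- That selection could never be detected. Preoperative characteristics are collected, and outcome can be related to predicted allocation. But the first pain score comes after surgery, when the exercise arm has already been trained, so it is not a clean baseline.

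**Conclusion.** The point holds as an avoidable weakness in allocation concealment, worth correcting because correction is nearly free. It is not evidence of bias. The firm part is the guess rate of about 69%, which needs only a single sequence and knowledge of past assignments. The share that is certain depends on a rule the protocol does not state: about 5.5% if sizes vary at random, 25–33% if one known size is used throughout. The bias is unknown; 0.03–0.05 SD to 0.19–0.38 SD is a range under assumed shifts of 0.5–1.0 SD, with the upper end near a worst case. That there is one sequence is inferred from the single hospital named and the absence of stratification factors.

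**What to change.** In Section 9.5:
- Remove the block sizes, and state that the restriction parameters are kept in a document held only by the independent consultant.
- State that each assignment is released by the online service already named, only after eligibility and consent have been irrevocably logged, and delete the envelopes. This also settles how the two mechanisms relate.
- Ask the consultant to consider a less predictable scheme with an undisclosed limit, for example big-stick with maximum imbalance 6. Hiding the block sizes takes away the certain predictions but leaves the 69% tally-based guess rate, so the scheme itself has to change if that rate is to fall. Other schemes would serve; the choice is partly one of preference.

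The cost is a wording change and, if the scheme changes, a new list from the same consultant, with no extra patients. The downside of big-stick is a possible imbalance of up to 6 patients, with negligible loss (34.7 against 35 per arm). Its limit must stay undisclosed, because some assignments become certain to anyone who knows it.

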#### **9.6 Masking**

Due to the nature of the intervention, participants and researchers cannot be blinded to group allocation. The treating healthcare professionals (i.e. the Research Nurse and Clinical Research Fellow) will also not be masked due to nature of the service. The surgeon will be masked to allocation. The data manager and trial statistician will be masked to allocation throughout the study.

### **10. Study period**

**Total research period:** IRB approval date ~ February 28, 2021

**Patient recruitment period:** IRB approval date - December 31, 2020

**Statistical processing and result report writing period:** 2 months from the date of completion of the last patient questionnaire

## 11. Research method

This study is for patients who are going to be prescribed facedown posture after retinal surgery.

Participating the study or not will not influence the clinical decision and surgical procedure, but only a pain assessment in the back neck, shoulder, and lower back will be additionally performed every day after the surgery for the study participants. Those who are assigned to the exercise group will additionally be instructed for a structured exercise program designed to keep the prone posture easily and to relieve musculoskeletal pain. The exercise group will be trained by an exercise therapist. All inpatient care and surgical procedures other than learning and performing rehabilitation exercise will be the same in both study groups.

| Control group                                                                                      | Exercise group                                                                                                                                                              |
|----------------------------------------------------------------------------------------------------|-----------------------------------------------------------------------------------------------------------------------------------------------------------------------------|
| After surgery, take and maintain facedown posture without getting additional training or exercise. | After surgery, subjects will be trained for a structured exercise routine by an exercise therapist and perform the exercise according to the instruction three times a day. |
| Pain assessment will be performed every day after surgery.                                         |                                                                                                                                                                             |

All patients scheduled for vitreoretinal surgery for macular hole or retinal detachment is going to be admitted to the hospital the day before surgery (day 1). On the day 1, every patients will be evaluated for their eligibility, and those who are eligible candidates will be provided with information about the trial and invited to participate. They will be given enough time to consider their decision and the opportunity to ask questions. After informed consent is obtained, subjects will be randomized.

On the day of the retinal surgery, an exercise therapist who is affiliated to the Department of physical and rehabilitation medicine, Samsung Medical Center, will visits before surgery to educate the structured

rehabilitation exercise program. Details of a structured exercise program for the exercise group is as follow.

Rehabilitation exercise education consists of **(1) proper facedown positioning**, which would assist patients to maintain the prone position more easily and stably without giving too much stress to the body, and **(2) facedown exercise**, which would reduce the burden on muscle and joints induced by the facedown posture and enhance muscle strength to withstand the stress applied by the facedown posture.

